## Abstract

**Introduction:**

Skeletal muscle dysfunction is central to both sarcopenia and physical frailty, which are associated with a wide range of adverse outcomes including falls and fractures, longer hospital stays, dependency and the need for care. Resistance training may prevent and treat sarcopenia and physical frailty, but not everyone can or wants to exercise. Finding alternatives is critical to alleviate the burden of adverse outcomes associated with sarcopenia and physical frailty. This trial will provide proof-of-concept evidence as to whether metformin can improve physical performance in older people with sarcopenia and physical prefrailty or frailty.

**Methods and analysis:**

MET-PREVENT is a parallel group, double-blind, placebo-controlled proof-of-concept trial. Trial participants can participate from their own homes, including completing informed consent and screening assessments. Eligible participants with low grip strength or prolonged sit-to-stand time together with slow walk speed will be randomised to either oral metformin hydrochloride 500 mg tablets or matched placebo, taken three times a day for 4 months. The recruitment target is 80 participants from two secondary care hospitals in Newcastle and Gateshead, UK. Local primary care practices will act as participant identification centres. Randomisation will be performed using a web-based minimisation system with a random element, balancing on sex and baseline walk speed. Participants will be followed up for 4 months post-randomisation, with outcomes collected at baseline and 4 months. The primary outcome measure is the four metre walk speed at the 4-month follow-up visit.

**Ethics and dissemination:**

The trial has been approved by the Liverpool NHS Research Ethics Committee (20/NW/0470), the Medicines and Healthcare Regulatory Authority (EudraCT 2020-004023-16) and the UK Health Research Authority (IRAS 275219). Results will be made available to participants, their families, patients with sarcopenia, the public, regional and national clinical teams, and the international scientific community.

**Trial registration number:**

ISRCTN29932357.

Strengths and limitations of this studySeeks to enrol older people with sarcopenia and physical prefrailty or frailty—an underserved group.Wide-ranging mechanistic studies embedded in the trial.Flexible recruitment methods and flexible study visits including option for participants to be seen at home.Limitations of short-term follow-up and small sample size.Will exclude some people with multimorbidity due to safety considerations.

## Background

Skeletal muscle dysfunction is central to both sarcopenia and physical frailty, which are common syndromes in older people. Sarcopenia, the loss of muscle strength and mass that commonly accompanies ageing^1^ is a major health problem for many older people. Sarcopenia is a major risk factor for falls, hospitalisation, increased length of stay, care home admission and earlier death.^2–4^ In addition, sarcopenia is an important component of the physical frailty syndrome, which is associated with a similar range of adverse outcomes.^5^ Physical frailty is typically defined as the presence of three or more of five physical characteristics (weight loss, low energy expenditure, exhaustion, slow gait speed and low grip strength).^6^ The presence of one or two of these characteristics indicates the presence of physical prefrailty as a precursor to physical frailty. Impaired physical performance is therefore a key characteristic of both sarcopenia and physical frailty and is a target for intervention that is prioritised by patients.^7^

At present, resistance exercise training is the only intervention proven to improve outcomes for people with sarcopenia or physical frailty, with limited evidence on its effects in physical prefrailty.^8–10^ Not all older people with sarcopenia or physical frailty are able or willing to undertake resistance training. As a result, alternative therapeutic options are needed to both prevent and improve sarcopenia and physical frailty, including through targeting physical prefrailty as a precursor state to more advanced physical frailty. Although the aetiology of sarcopenia and physical frailty are incompletely understood, it is becoming clear that multiple fundamental biological pathways related to ageing are important in driving these syndromes. Key pathways include inflammation, mitochondrial dysfunction, neuromuscular junction dysfunction, cellular senescence, and dysregulation of nutrient sensing and intracellular metabolism.^1 11^

Metformin, a biguanide molecule, has been used as a treatment for type 2 diabetes mellitus for decades; it is a generally safe and well-tolerated therapy even in older people with physical frailty or multiple health conditions. Importantly, the mode of action of metformin in lowering glucose in patients with type 2 diabetes does not rely on stimulating insulin release, and thus users are not subjected to an increased risk of hypoglycaemia. Metformin has pleiotropic effects on glucose metabolism and energy utilisation as well as on a range of other age-related pathophysiological pathways; several of these actions may be beneficial in treating the muscle dysfunction seen in sarcopenia and physical frailty as summarised in figure 1.^12–23^ Not all mechanisms of action of metformin may be beneficial however. Some pathways (eg, adenosine monophosphate kinase activation) are similar to those triggered by caloric restriction,^24^ which while potentially beneficial for longevity over a long period may have adverse catabolic consequences in the shorter term. It is only by testing metformin in older people with sarcopenia that the balance of benefits and risks can be properly assessed.

**Figure 1 F1:**
[figure not shown]
Potential mechanisms of action through which metformin could improve skeletal muscle function. AMP Kinase, Adenosine MonoPhosphate activated protein Kinase; mTOR, mammalian Target Of Rapamycin.

Observational studies show lower rates of cardiovascular events and cancer mortality in metformin users,^25 26^ consistent with a wide range of physiological effects as outlined above. Few studies have examined the relationship between metformin use, sarcopenia and physical frailty. Such observational studies are challenging because metformin is currently indicated for use in diabetes mellitus—itself implicated in accelerated ageing, skeletal muscle dysfunction and earlier onset of physical frailty. However, incident and prevalent frailty-related diseases (including falls, weight loss, gait disorders and frailty diagnosed using a cumulative deficits Frailty Index, FI) have been found to be less common in patients with type 2 diabetes treated with metformin compared with those treated with other glucose-lowering agents in observational studies.^26 27^

One previous trial conducted in Indonesia studied people aged 60 and over with prefrailty (defined by either the Fried criteria or by a cumulative deficits index) but without diabetes.^28^ Participants were randomised to receive 16 weeks of 500 mg metformin thrice daily or matched placebo. Walk speed increased significantly in the treatment group compared with placebo (by 0.13 m/s; which exceeds the minimum clinically important difference of 0.10 m/s^29^). The recent MASTERS randomised trial did not show evidence that metformin enhanced the effect of resistance training, but the focus of this trial (augmentation of resistance training) was different and did not target people with sarcopenia or physical frailty.^30^

### Trial objectives

MET-PREVENT is a parallel group, randomised, double-blind, placebo-controlled trial. The primary objective of MET-PREVENT is to provide proof of concept evidence as to whether metformin is superior to placebo in improving physical performance in older people with sarcopenia and physical prefrailty or frailty. The secondary objectives are to elucidate potential mechanisms of action of metformin on sarcopenia and physical frailty by correlating changes in biomarkers with changes in physical performance measures between baseline and 4 months. A placebo-controlled design has been selected to minimise bias and is appropriate given the absence of other pharmacological interventions for sarcopenia or physical frailty.

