### Sample size

Based on previous work, we assumed a minimum clinically important difference for the four metre walk speed of 0.1 m/s.^28^ Assuming a SD of 0.24 as seen in the English Longitudinal Study of Ageing,^47^ and a correlation between baseline and 6-month measures of 0.8, as seen in a recent trial of older people at risk of falls^48^ (a similar population to those who will be enrolled in this trial), a total of 66 participants would be needed (33 per group) to give 80% power to detect this difference at a two-sided alpha=0.05 in an analysis that is adjusted for baseline values. Recruiting 80 participants will allow for 17.5% drop-out (higher than observed in previous trials of spironolactone and of vitamin D in similar populations^49 50^) to give 66 participants at follow-up.

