Although the trial is powered to detect the minimum clinically important difference in four metre walk speed, it is not powered to detect clinically important differences for some of the secondary outcomes. However, the trial seeks to provide proof-of-concept for a larger, multicentre trial that would be powered to detect differences in these outcomes, including transitions from physical prefrailty to frailty. The trial population excludes some groups for safety reasons (eg, those with chronic kidney disease) which limits the generalisability of the results. Muscle biopsies are not being performed, thus direct information on changes in skeletal muscle structure and function will not be obtainable from this trial.

The collection of blood and stool samples for future mechanistic analyses will maximise the scientific value of the trial but also look to identify those groups that may be more likely to benefit from metformin as an intervention in a future large trial. In addition, the mechanistic analyses (which will be performed after the main trial is complete) will identify which mechanistic pathways are most important in mediating any benefit of metformin and in doing so will help us identify pathways and featured targets for other interventions to prevent or treat sarcopenia and physical frailty. We believe that this study design provides a template for other phase II intervention trials for sarcopenia and physical frailty; this template should both accelerate progress in translational research and also enable easier comparison of results across different trials.^54^

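### The mechanism objective is tied to a change-change correlation that ignores the randomised contrast, and the Discussion claims more from it than it can show

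*Protocol article*

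**What the plan says.** Under Trial objectives, the protocol article gives an aim and the method meant to serve it. The aim is "to elucidate potential mechanisms of action of metformin on sarcopenia and physical frailty". The method is "correlating changes in biomarkers with changes in physical performance measures between baseline and 4 months". The sentence does not mention treatment arm, an effect of metformin on the biomarker, or mediation.

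The Discussion describes the same work more strongly: the mechanistic analyses, to be done once the main trial is over, "will identify which mechanistic pathways are most important in mediating any benefit of metformin". They are then expected to point to targets for other interventions.

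Two other sections bear on this. Secondary outcome measures counts mechanistic outcomes among the secondary outcomes. It also says that blood is stored for later measurement of a panel of cytokines, senescence markers and oxidative-stress markers, with no number given, and that stool is stored for microbiome work. Statistical analysis plans to treat continuous secondary endpoints like the primary outcome, that is, by regression comparing arms, adjusted for the baseline value of the outcome, baseline walk speed and sex.

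**The concern.** Randomisation protects the comparison between arms. It does not protect an association between two changes that both occur after randomisation. An infection or a fall during the four months could plausibly raise an inflammatory marker and slow walking in either arm. The two changes would then correlate whether or not metformin did anything.

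For a biomarker to mediate a benefit, metformin must move it and it must in turn affect performance. The method named in the objective addresses neither step. A reader who follows the objective as written could therefore attribute ordinary co-variation in frail older people to the drug. The Discussion would have that attribution guide the choice of pathways and targets for later trials.

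**Working it through.** **The plan's own figure.** The only sample size calculation is for the primary outcome. Its inputs, all from Sample size, are: "we assumed a minimum clinically important difference for the four metre walk speed of 0.1 m/s"; "Assuming a SD of 0.24 as seen in the English Longitudinal Study of Ageing"; "a correlation between baseline and 6-month measures of 0.8".

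- Baseline-adjusted SD = 0.24 × √(1 − 0.8²) = 0.144 m/s.
- n per arm = 2 × [0.144 × (1.960 + 0.842) / 0.1]² = 32.6, so 33 per arm and 66 in total, with power 80.5%.
- 66 / (1 − 0.175) = 80.

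This reproduces the stated 66 analysed and 80 recruited and is not in dispute. No power is claimed for the correlations.

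**Threshold for a correlation at N = 66.** The two-sided 5% critical value of t on 64 df is 1.998, so |r| is significant above 1.998 / √(64 + 1.998²) = 0.242.

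**Chance of a significant correlation if metformin has no effect on anything.** This is the power to detect the natural correlation ρ between the two changes. The document gives no ρ, so it is assumed and varied. By the Fisher approximation the chance is about Φ(atanh(ρ) × √63 − 1.96). At ρ = 0.2 this is Φ(0.2027 × 7.937 − 1.96) = Φ(−0.35) = 36%. Simulation with 40,000 trials per setting gives:

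| Assumed ρ | Pooled correlation | Adjusted for arm |
|---|---|---|
| 0 | 5% | 5% |
| 0.1 | 13% | 12% |
| 0.2 | 37% | 36% |
| 0.3 | 70% | 69% |
| 0.4 | 92% | 92% |

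Adjusting for arm does not remove the problem. A between-arm test of the biomarker is positive 5% of the time whatever ρ is.

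**One concrete source of co-variation: a shared illness.** All illness inputs are assumptions. The SD of walk-speed change follows from the Sample size inputs: 0.24 × √(2 × (1 − 0.8)) = 0.152 m/s. Metformin has no effect.

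| Share ill | Slowing (m/s) | Biomarker rise | SD of biomarker change | Significant |
|---|---|---|---|---|
| 20% | 0.15 | 1 | 1 | 19% |
| 10% | 0.15 | 1 | 1 | 10% |
| 5% | 0.15 | 1 | 1 | 7% |
| 20% | 0.075 | 0.5 | 1 | 6% |
| 20% | 0.15 | 1 | 0.63 | 36% |

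The range over these settings is 6% to 36%. It is not a bound: the last row with 30% ill gives 51%.

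**Several biomarkers.** Even at ρ = 0, at least one of k independent tests is positive with probability 1 − 0.95^k: 23%, 40% and 64% for k = 5, 10 and 20. The panel size is not stated, so k is also an assumption.

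**Metformin active, biomarker not a mediator.** Suppose metformin improves walk speed by 0.1 m/s (0.1 / 0.152 = 0.66 SD of change) and moves the biomarker by 0.5 or 1.0 SD through an unrelated route. The pooled correlation is then significant in 9% or 21% of trials, although the biomarker mediates nothing.

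**The case against.** The strongest objection is that a valid analysis is already planned. Mechanistic outcomes are secondary outcomes, and the Statistical analysis section gives continuous secondary endpoints a between-arm model with the covariates one would ask for. This stands, with a limit. The section plainly reaches measures such as HbA1c, HOMA-IR, skin AGE and lean mass. Whether it reaches the assays on stored samples is unclear, and nothing connects it to the mechanism objective. A reader might infer that the mechanistic conclusions rest on correlations alone, or that randomised evidence on biomarkers is ignored; the document does not support that.

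Second, the objective is one sentence in a condensed article, it says only that potential mechanisms will be studied, and an analysis plan that is not shown may add arm or a mediation model. This also stands as far as it goes: missing detail is not the point here. But the sentence does name a method, and the hedge in the objective does not carry over to the unqualified statement in the Discussion.

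Third, a reader might infer that these correlations would often be positive with an inert drug. That is too strong. With no natural co-variation a single test is positive 5% of the time, and with rarer or smaller illness effects the rate is 6% to 10%. The document supplies neither the co-variation nor the number of biomarkers.

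Finally, a mediation model is no cure by itself. The biomarker is not randomised, so the same illness could confound its relation with performance within arms. Requiring a significant biomarker effect before fitting such a model would also be a poor filter. At 33 per arm, 80% power needs a between-arm difference of 0.69 SD unadjusted, or 0.60 and 0.41 SD with baseline correlations of 0.5 and 0.8, so real mechanisms could be discarded.

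**Conclusion.** The point holds in a limited form. The method named for the mechanism objective does not use the randomised contrast, and the Discussion's claim to identify mediating pathways exceeds what that method can support. How often it would mislead depends on quantities the document does not give: 5% per test with no natural co-variation, and 13%, 37% and 70% at assumed correlations of 0.1, 0.2 and 0.3 with 66 analysed.

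This is a matter of linking analyses and matching claims to method. The primary outcome analysis, the sample size and the data collection are unaffected.

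**What to change.** - In Trial objectives, state that the mechanism objective is addressed first by the between-arm effect on each biomarker, explicitly including the stored-sample assays. Use the model already in Statistical analysis, adjusted for baseline biomarker, baseline walk speed and sex.
- Label the change-change correlations as descriptive.
- Report any mediation model as exploratory. Include arm and the baseline values, state the assumption of no unmeasured confounding between biomarker and performance, and do not make it conditional on a significant biomarker effect.
- In the Discussion, replace the promise to identify mediating pathways with one to generate hypotheses about them.

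The cost is some rewording, slightly more analysis on the same samples, and a more modest mechanistic claim. The mechanistic work follows the main trial, so the change need not delay the primary analysis.

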## Methods: participants, interventions and outcomes

### Trial setting

Participants will be recruited from the catchment areas of two secondary care hospitals in the North-East of England. Participants will be approached through Older Peoples Medicine Clinics, Day Units, assessment units and rehabilitation facilities at the hospitals. In addition, local general practices (GPs) will act as participant identification centres, a registry of patients with sarcopenia^31^ and the National Institute for Health and care Research BioResource will be used to identify additional potential participants. A flexible approach to the setting for participation will be offered, with the option of either research centre, clinic or the participant’s own home as the setting for trial visits.

### Eligibility criteria

The target population for MET-PREVENT is older adults (≥65 years) with sarcopenia and either physical prefrailty or frailty. Sarcopenia is defined using the handgrip strength and sit to stand thresholds from the 2019 European Working Group on Sarcopenia in Older People (EWGSOP) guidance.^32^ Low muscle mass is not used as an eligibility criterion in this trial; the 2019 EWGSOP guidance allows a diagnosis of probable sarcopenia without muscle mass measurement. Muscle mass is not routinely measured in clinical practice, and the omission of this criterion will improve the relevance of the trial results to clinical practice. Physical prefrailty and frailty are defined following the method of Fried *et al*^6^; participants will have a minimum of two of the five Fried criteria (and thus fulfil the definition for prefrailty) but may have three or more criteria (fulfilling the definition of frailty). The MET-PREVENT eligibility criteria are listed in box 1. Exclusion criteria are primarily designed to exclude participants at higher risk of adverse events (AEs) from taking metformin, those where metformin therapy is already indicated (eg, diabetes mellitus) and other types of skeletal myopathy (eg, steroid myopathy, heart failure myopathy) where confusion with sarcopenia might arise.

Box 1MET-PREVENT inclusion and exclusion criteriaInclusion criteriaAdults aged ≥65 years.Low maximum handgrip strength (<16 kg for women, <27 kg for men) OR 5× sit to stand time >15 s.Slow walk speed (<0.8 m/s on 4 me walk test).Exclusion criteriaDiabetes mellitus (type 1 or type 2).Previous intolerance of metformin or taking metformin for another condition.Any contraindication to metformin, as listed in the current summary of medicinal product characteristics for metformin.Any medication which significantly interacts with metformin, as listed in the current summary of medicinal product characteristics for metformin.Estimated glomerular filtration rate <45 mL/min/1.73 m^2^ by the Modified Diet in Renal Disease 4 (MDRD4) or Chronic Kidney Disease - EPIdemiology collaboration (CKD-EPI) equation.History of diarrhoeal illness within the last three months (>48 hours of Bristol stool chart grade 6 or 7).Alcohol intake >21 units/week (women) or >35 units/week (men).Symptomatic chronic heart failure, diagnosed according to European Society of Cardiology guidelines (asymptomatic left ventricular systolic dysfunction will not be an exclusion criterion).Liver function tests (bilirubin, alanine aminotransferase or alkaline phosphatase) >3× upper limit of normal.Oral steroid dose >7.5 mg prednisolone equivalent per day.Unable to mobilise without human assistance.Unable to give written informed consent.Life expectancy of <3 months as adjudicated by the local Investigator.Participation in other interventional studies within 30 days prior to trial entry. Coenrolment with other interventional studies is not allowed (observational studies and registries are permitted.

### Interventions

All randomised participants will take either metformin hydrochloride (500 mg film-coated) tablets or matched placebo tablets, orally, three times a day with food or just after a meal. No dose adjustments are planned. Study medication is dispensed in a single bottle which is identical for metformin and placebo.

Investigators may discontinue the trial treatment in the event of side effects occurring, that are possibly, probably or definitely related to trial medication and which are not tolerable to the participant, or which constitute a serious adverse reaction (SAR) or suspected unexpected SAR. Treatment will also be discontinued if the participant requests the medication to be withdrawn; in the event of a new diagnosis of diabetes mellitus (type 1 or type 2) or symptomatic chronic heart failure; if the estimated glomerular filtration rate (GFR) falls below 30 mL/min/1.73 m^2^ or plasma lactate concentration is>4 mmol/L in the safety follow-up visit blood tests, or if lactic acidosis is diagnosed as part of clinical workup for an intercurrent illness. The trial medication may be temporarily discontinued at the instigation of the treating clinical team or the study team if an episode of acute kidney injury or an intercurrent illness with a risk of dehydration or hypovolaemia occurs. Once this has resolved, trial medication may be restarted if the estimated GFR is >30 mL/min/1.73 m^2^. Participants who discontinue allocated trial medication and wish to remain in the trial will be followed up as per their allocated treatment intervention arm. If a participant does not want to attend any further trial visits but is willing to complete questionnaires by phone/post then they may continue in the trial.

